### Objectives

The primary objective of this RCT focus on the usefulness of the proposed home-based VR intervention for decreasing stress and anxiety and for enhancing the knowledge about these conditions compared to a control group. The secondary objective is to assess the acceptability of the home-based VR training.

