	**Study period**					
	**Enrolment**	**Baseline**	**Allocation**	**Intervention**	**Post-intervention**	**Follow-up**
**Timepoint (weeks)**	** − 1**	**0**	**0**	**0**	**1**	**5**
Enrolment:						
Eligibility screen	X					
Informed consent	X					
Allocation			X			
Interventions						
Experimental group				↔		
Control group				↔		
Assessments:						
Demographics		X				
Use of technological solutions and VR		X				
Level of exposure to COVID-19		X				
FCOR		X				
Stress and anxiety management		X				
PSS-10		X			X	X
STAI-Y2		X			X	X
DASS-21		X			X	X
Knowledge of stress and anxiety		X			X	X
STAI-Y1				X		
VAS-A				X		
SUS					X	
SDM					X	
NPS					X	
Difficulties and adverse effects					X	
Interview					X	

*FCOR* Fear of Coronavirus, *PSS-10* Perceived Stress Scale, *STAI-Y2* State-Trait Anxiety Inventory Form Y-2, *DASS-21* The Depression, Anxiety and Stress Scale-21 Items, *STAI-Y1* State-Trait Anxiety Inventory Form Y-1, *VAS-A* Visual Analogue Scale for Anxiety, *SUS* System Usability Score, *SDM* Subjective Difficulty Measure, *NPS* Net Promoter Score

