### Outcomes

#### Primary outcome measure

At baseline, post-intervention, and follow-up, participants in the experimental and in the control group will complete the following questionnaires that will serve as the primary outcome measures:*Perceived Stress Scale* (PSS-10) [77, 78]: the PSS is a 10-item self-reported measure to assess the current stress level using a 5-point Likert scale.*State-Trait Anxiety Inventory Form Y-2 (STAI-Y2)* [79, 80]: a validated and widely used measure of trait anxiety. Individuals are asked to specify to which extent, on a 4-point Likert scale (from “not at all” to “very much”), they usually perceive each of the 20 indicated feelings.*The Depression, Anxiety and Stress Scale-21 Items (DASS-21)* [81]: is a set of three self-report scales designed to measure depression, anxiety, and stress symptoms. Each of the three scales contains seven items, divided into subscales with similar content. The scores for depression, anxiety, and stress are calculated by adding up the scores for the relevant items.Ad hoc* questionnaire on the knowledge of stress and anxiety*: individuals are asked to rate on a 7-point Likert scale (1 = “not at all,” 7 = “very much”) knowledge about the differences between anxiety and stress, causes and symptoms of stress and anxiety, and techniques for the management of these conditions. Besides, participants complete 5 factual questions in multiple-choice format (e.g., “Which is the first phase of the General Adaptation Syndrome?”) and 2 conceptual questions in short-answer format (e.g., “What are the three main categories of stress symptoms?”). The questions are based on the methodology used in a previous study (Parong and Mayer, 2018) (see Table 4).

**Table 4 Tab4:** The ad hoc questionnaire on the knowledge of stress and anxiety

Questionnaire on the knowledge of stress and anxiety
***Part 1. Rate on a 7-point Likert scale (1***** = *****“not at all,” 7***** = *****“very much”) your level of knowledge about*****:** • The differences between anxiety and stress • Causes and symptoms of stress and anxiety • Techniques for the management of stress and anxiety

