### Data analysis

Analysis of variance will be used to evaluate baseline characteristics of the two groups involved in the study, the overall significance of improvement across primary outcome measures, and drop-out versus maintainers. Categorical variables will be compared using Fisher or chi-square tests and continuous variables using *t*-test or Mann–Whitney tests, as appropriate. To assess the effectiveness of the intervention, groups will be compared with a 2 × 2 repeated measure mixed ANOVA for the pre- and post-primary outcome measures (factor Group X factor Time: pre and post). The analysis will be performed for the PSS, STAY-Y2, and DASS-21. A repeated-measures ANOVA (factor Group × factor Time: day of the week) will compare treatment effects within the 1-week intervention for the STAY-Y2 and the VAS-A. Tests of statistical significance and confidence intervals will be two-sided. A *p* < 0.05 will be considered statistically significant. Descriptive methods will be used to report the usability of the intervention for the secondary outcome intervention (i.e., SUS, SDM, NPS, ad hoc questionnaire on difficulties and adverse effects). Data analyses will be carried out through SPSS software.

Recordings from the post-intervention interviews will be transcribed. Two researchers will read the interview transcripts carefully several times to have a sense of the whole data, identifying emerging themes and categories [87]. A codebook will be created and modified until the final set of codes is obtained and reached to the data saturation point when there is no emergence of other new themes. Qualitative data analysis will be conducted using a thematic content analysis approach following a systematic process. Codes will be applied to the transcripts and converted into categories to represent the main themes arising from the data [88]. Triangulation of themes and concepts will be used to compare further and contrast the data from the different participating groups. Codes will be applied to the transcripts and converted into categories to represent the main themes arising from the data [88].

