### Discussion

The main aim of this RCT study is to evaluate the usefulness and the acceptability of a brief home-based VR training for the management of stress and anxiety in healthcare workers. Since stress and anxiety have increased after the outbreak of the COVID-19 crisis [4–7] and given that these conditions can have harmful effects on both health and work performance [17, 18, 20, 21], the study’s findings may offer valuable insights for developing innovative psychological interventions to help hospital staff.

If our brief home-based VR training will produce a significant decrease in stress and anxiety and an increase in the knowledge of these conditions, it could become an empirically assessed viable option for protecting the mental health of healthcare workers both during the pandemic and once the emergency ends. Furthermore, it could easily be adapted to other categories of people who need support in managing stress and anxiety. Indeed, the proposed intervention is characterized by the fact that it uses free and ready-to-use virtual experiences, available in different languages, including English (e.g., MIND-VR and The Secret Graden). For example, the proposed VR intervention can be used within programs to manage stress and anxiety for all those people forced into isolation or an extended hospital stay due to COVID-19 infection or other physical disorders. Also, since Summer 2021, this type of approach has been tested in collaboration with a Canadian university and an Italian hospital, respectively, to train future doctors and nurses and provide psychological support to families of patients with dementia.

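### Knowledge of stress and anxiety is a primary objective and a primary outcome, but the effectiveness analysis does not name it and no knowledge score is defined

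*Protocol article*

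**What the plan says.** Four places in the protocol article treat knowledge as a main question of the trial.

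- **Objectives.** The primary objective covers reducing stress and anxiety and also "for enhancing the knowledge about these conditions compared to a control group".
- **Primary outcome measure.** Participants in both arms "will complete the following questionnaires that will serve as the primary outcome measures". Four instruments follow: PSS-10, STAI-Y2, DASS-21 and the ad hoc knowledge questionnaire. The last has three self-ratings on a 7-point scale, then "participants complete 5 factual questions in multiple-choice format", then two short-answer questions (Table 4).
- **Assessment schedule (Table 2).** Knowledge is collected at baseline, post-intervention and follow-up, like the other three.
- **Discussion.** The intended conclusion depends on "a significant decrease in stress and anxiety and an increase in the knowledge of these conditions".

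The Data analysis section introduces the effectiveness comparison in general terms: "groups will be compared with a 2 × 2 repeated measure mixed ANOVA for the pre- and post-primary outcome measures". The next sentence but one words away from it is specific: "The analysis will be performed for the PSS, STAY-Y2, and DASS-21". Knowledge is named neither there nor anywhere else in that section, although the usability measures and the interviews each have a stated analysis.

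**The concern.** The article declares four primary measures and lists three for the effectiveness test. This is not a detail left to a statistical analysis plan that we cannot see. The article itself gives a list, and the list disagrees with its own objective and outcome sections. Two readers could reach opposite conclusions about whether a primary outcome is tested.

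Two things are at stake. First, the knowledge questionnaire is the outcome most directly tied to the psychoeducation component, which is one of the two features (with home use) that the article says set this training apart from earlier VR programmes. Second, a knowledge result reported later without a named test and a named score would be open to the charge that the analysis, or the part of the questionnaire, was chosen after the data were seen.

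**Working it through.** **1. Passages side by side**

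| Primary measure | In primary objective | Listed as primary outcome | Baseline, post, follow-up | Named for the 2 × 2 ANOVA |
|---|---|---|---|---|
| PSS-10 | yes (stress) | yes | yes | yes |
| STAI-Y2 | yes (anxiety) | yes | yes | yes (spelled STAY-Y2) |
| DASS-21 | yes (stress, anxiety) | yes | yes | yes |
| Knowledge questionnaire | yes | yes | yes | **no** |

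The mismatch is one of four measures.

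**2. What would enter the model.** The instrument yields at least three candidate scores: three self-ratings, five multiple-choice items and two open answers. The article names neither a total nor a lead part. Adding the word knowledge to the list would therefore not by itself define a variable to analyse.

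**3. The plan's own sample size.** Inputs from the Sample size section: f = 0.25, alpha = 0.05, 2 groups, power 0.95, stated N = 54. From Data analysis: m = 2 time points. Assumed: correlation ρ = 0.5 between time points, because the article gives none.

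- Noncentrality for the Group × Time interaction: λ = N f² m / (1 − ρ) = 54 × 0.0625 × 2 / 0.5 = 13.5, with 1 and 52 degrees of freedom.
- Power = 0.950, so the stated 54 is reproduced. At N = 60, λ = 15.0 and power = 0.968.
- N depends on ρ: 106 at ρ = 0, 76 at 0.3, 34 at 0.7.

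The calculation is per outcome, so analysing knowledge with the same model leaves it unchanged.

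**4. Price of adding a fourth test at 0.05.** Chance of at least one false positive, tests taken as independent (an assumption):

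- One test per questionnaire: 1 − 0.95³ = 0.143 becomes 1 − 0.95⁴ = 0.185.
- DASS-21 counted as three subscales: 1 − 0.95⁵ = 0.226 becomes 1 − 0.95⁶ = 0.265.

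**5. Price of leaving the score open.** Suppose one of three knowledge scores could be chosen after the fact. A two-sided test at 0.05 gives a false result in favour of VR with probability 0.025.

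- Independent scores: 1 − 0.975³ = 0.073.
- Pairwise correlation 0.5 (normal scores): 0.063.
- One score fixed in advance: 0.025.

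The number of scores and the correlations are assumptions. The contradiction in step 1 does not depend on them.

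**The case against.** The strongest defence is that the Data analysis section does cover knowledge, in general words. It opens by assigning analysis of variance to overall improvement on the primary outcomes, and the 2 × 2 sentence also refers to primary outcome measures, which by the article's own definition include the knowledge questionnaire. On this view the three-item list is a drafting slip. Part of this stands: the text is ambiguous, and a slip is quite possible. But the opening sentence gives no outcome, time points or group contrast, and the list narrows the 2 × 2 sentence. Neither supplies a named between-group test of knowledge.

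A reader might go further and infer that the trial cannot answer its knowledge question at all. The documents do not support that. The data are collected in both randomised arms at three times, so the question remains answerable; what is missing is a named test and a named score.

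A reader might also put the selection risk at 14% (three independent scores) or about 12.5% (correlation 0.5). Those figures count false positives in either direction, whereas the worry is a choice that favours VR. The matching figures are about 7% and 6%, and they measure selective scoring, not the omission.

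Finally, one might object that the open answers will be scored by someone who knows the allocation. The article says that participants learn their group, but not who scores these answers or under what masking. A condensed article commonly leaves this to the full protocol, so it is no finding here. The same applies to the details of a scoring key.

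**Conclusion.** The point holds as an internal contradiction. Knowledge is primary in the objective, the outcome list and the intended conclusion, and it is absent from the stated list of outcomes for the effectiveness analysis. The supportable statement is that a primary outcome has no named between-group test and no single named score.

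This rests on comparing the article's sections, not on a calculation. The numbers serve only to size the consequences: about 6–7% instead of 2.5% for a false finding in favour of VR if the score is chosen from three afterwards (assumed correlation 0.5 to 0), and a rise from about 0.14 to 0.19 in the chance of any false positive once a fourth independent test is added. The sample size of 54 is not affected; its reproduction rests on the assumed correlation of 0.5.

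**What to change.** Either of two repairs resolves the contradiction.

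1. **Keep knowledge primary.** Change the sentence in Data analysis so that the list reads: PSS-10, STAI-Y2, DASS-21 and the knowledge score. Use the same Group × Time model as for the others. State in advance the one score that enters it. A reasonable choice is the factual score from Parts 2 and 3 of the questionnaire, marked against a fixed key, with the Part 1 self-ratings as supportive. The article ranks none of the parts, so another single score would also serve if it is fixed before the data are examined.
2. **Drop knowledge from the primary tier.** Remove it from the primary objective and the primary outcomes, and align the conclusion foreseen in the Discussion.

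The first repair costs a sentence or two plus the scoring key, and no extra participants. Its statistical price is one more primary test at 0.05, which should be acknowledged alongside the change. The second costs no extra test but gives up knowledge as a primary claim.

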**Methods:**

The study is a randomized controlled trial. It includes two groups of 30 individuals recruited from healthcare workers: (1) the experimental group and (2) the control group. Participants in the experimental group will receive a training consisting of three home sessions performed in a week. In each session, participants will try through an immersive virtual reality standalone system (i.e., Oculus Quest 2) a virtual psychoeducation experience on stress and anxiety (i.e., MIND-VR). Subsequently, they will try the virtual relaxation content (i.e., The Secret Garden). The control group will receive no training and will be reassessed one week and one month after the initial evaluation.

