#### Experimental group

Participants in the experimental group will receive the home-based VR intervention. Following a description of the protocol in detail:*Intake session (session 1):* after signing the informed consent and completing the baseline questionnaire accessible online (i.e., demographic, ad hoc questionnaire about the use of technological solutions and VR, ad hoc questionnaire on the level of exposure to COVID-19, FCOR, ad hoc questionnaire on stress and anxiety management, PSS-10, STAI-Y2, DASS-21, ad hoc questionnaire on knowledge of stress and anxiety), participants will receive from the research psychologist an explanation about the aims and methods of the home-based VR program. Participants will be asked for their involvement and availability during a week to allow in-home training. The psychologist will remind participants to perform the training three per week, with a distance of 2 days between one session and another. Then, individuals will receive information about the safety and hygiene procedures to prevent COVID-19 infection (see Table 3). The psychologist will give participants the Oculus Quest 2, a consumer-grade standalone VR system that consists of an HMD and two controllers. Individuals will wear the headset and receive a short 15-min training on using the VR system. In particular, they will try the tutorial content available on the Oculus Store. Furthermore, individuals will receive a link to complete the online questionnaires (i.e., STAI-Y1, VAS-A) before and after each session. They will be provided with a log book in which to record technical problems, safety issues, and the date and time they used VR during the intervention. Finally, the research psychologist will schedule the date of the post-training session.*Training sessions (sessions 2, 3, and 4):* they will consist of three home sessions of approximately 30 min each, conducted in a week with a distance of 2 days between one session and another. Participants will try for about 15 min one path of the virtual psychoeducational experience MIND-VR in each session (see Fig. 2). Subsequently, they will use for about 10 min the virtual relaxation content The Secret Garden. Individuals will be asked to complete online the VAS-A and the STAI-Y1 at the beginning and the end of each session.*Post-training session (session 5):* the research psychologist will meet participants for the post-intervention interview at the end of the training. On this occasion, participants will return the Oculus Quest 2, which will undergo specific procedures to avoid contamination by COVID-19. Participants will be asked to complete within 1 week after completion of the intervention the online questionnaires (i.e., PSS-10, STAI-Y2, DASS-21, ad hoc questionnaire on knowledge of stress and anxiety, SUS, SDM, NPS, ad hoc questionnaire on difficulties and adverse effects).*Follow-up session (session 6):* the PSS-10, STAI-Y2, DASS-21, and the ad hoc questionnaire on knowledge of stress and anxiety will be conducted after a 1-month follow-up.

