#### Control group

This group will undergo baseline, post-intervention, and follow-up assessments without undergoing any training during the 1-week intervention period.

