**Part 2. Rate on a 7-point Likert scale (1 = “not at all,” 7 = “very much”):** • How important in general do you think to have psychological support for stress management and anxiety concerning your profession? • How important do you think it is to have psychological support for managing stress and anxiety in times of emergency, such as those experienced during the COVID-19 crisis? • How important do you feel to follow a stress and anxiety management program at this time in your life? • Have you ever attended meetings about stress and anxiety? • Have you ever searched the Internet for information on stress and anxiety? • Have you ever read books on stress and anxiety?

Besides, with the aim of measuring changes in the affective states of individuals during the intervention, participants of the experimental group will be asked to fill before and after each of the training session the following self-report questionnaires:*State-Trait Anxiety Inventory Form Y-1* (STAI-Y1) [79, 80]: STAY-Y1 addresses state anxiety, which could be defined as a temporary emotional condition characterized by apprehension, tension, and fear about a particular situation or activity. This inventory consists of 20 items on a 4–4-point Likert scale, like the STAI-Y2.*Visual Analogue Scale for Anxiety* (VAS-A) [85, 86] is an instrument that measures state anxiety across a continuum. It is a horizontal line, 100 mm in length, anchored by word descriptors at each end (“no anxiety”; “very severe anxiety”). Individuals mark on the line the point that they feel represents their perception of their current state. The VAS-A score is determined by measuring in mm from the left-hand end of the line to the point that the person marks.

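### The Group × day ANOVA planned for the intervention week cannot compare treatment effects, because only the experimental group is measured in that week

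*Protocol article*

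**What the plan says.** The Data analysis section sets out two longitudinal models. The first, for effectiveness, is a 2 × 2 mixed ANOVA (group by pre/post) on the PSS, STAI-Y2 and DASS-21. The second covers the intervention week: "factor Group × factor Time: day of the week) will compare treatment effects within the 1-week intervention for the STAY-Y2 and the VAS-A".

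The measurement schedule appears in several places:

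- **Other measures**, introducing STAI-Y1 and VAS-A: "participants of the experimental group will be asked to fill before and after each of the training session the following self-report questionnaires".
- **Experimental group**, training sessions: "Individuals will be asked to complete online the VAS-A and the STAI-Y1 at the beginning and the end of each session". The training is "three home sessions of approximately 30 min each, conducted in a week with a distance of 2 days between one session and another".
- **Control group**: "This group will undergo baseline, post-intervention, and follow-up assessments without undergoing any training during the 1-week intervention period". The abstract agrees: "The control group will receive no training and will be reassessed one week and one month after the initial evaluation".
- **Primary outcome measure**, a list that includes STAI-Y2: "At baseline, post-intervention, and follow-up, participants in the experimental and in the control group will complete the following questionnaires". STAI-Y2 is described there as "a validated and widely used measure of trait anxiety".
- **Table 2** puts STAI-Y2 at baseline, post-intervention and follow-up, and puts STAI-Y1 and VAS-A in the intervention column only.

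**The concern.** A Group × Time analysis needs repeated measurements of the same outcome in both groups. For the intervention week the article schedules such measurements in one group only, and one of the two scales named for the analysis is not given in that week. The sentence nevertheless says that the model will compare treatment effects.

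An analyst who follows the plan will find no control data and will have to drop the analysis or improvise. The obvious substitute is the before/after change in the experimental arm. That change mixes any effect of the VR session with expectation, repeated testing and the passage of time. Because the plan already calls the result a treatment effect, the substitute could be reported under a label it cannot support.

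**Working it through.** **Step 1. Data by arm and occasion** (30 per group, from the abstract; schedule from Table 2 and the sections cited above).

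| Scale | Experimental, in week | Control, in week | Both arms at baseline, post-intervention and follow-up |
|---|---|---|---|
| VAS-A | 3 sessions × 2 = 6 per person | 0 | no |
| STAI-Y1 | 3 sessions × 2 = 6 per person | 0 | no |
| STAI-Y2 | 0 | 0 | yes |

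The maximum number of in-week records per scale is 30 × 3 × 2 = 180 for VAS-A and STAI-Y1, all in the experimental arm. STAI-Y2 has in-week data for 0 of 60 participants.

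**Step 2. Can the Group terms be estimated?** Take one record per session, with G = 1 for the experimental group and D2, D3 marking the second and third sessions:

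y = b0 + b1·G + b2·D2 + b3·D3 + b4·G·D2 + b5·G·D3 + error.

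Every observed row has G = 1. The column for G then equals the intercept, G·D2 equals D2, and G·D3 equals D3. With 30 × 3 = 90 rows the design matrix has 6 columns and a computed rank of 3. Only the sums b0 + b1, b2 + b4 and b3 + b5 can be estimated, which is the time course within the experimental arm. The Group effect b1 and the interaction terms b4 and b5 cannot be separated from the rest. Reading Time as six occasions, or as calendar days, changes nothing, because G is still constant.

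**Step 3. Does correcting the scale name help?** Reading STAI-Y2 as STAI-Y1 supplies in-week records in the experimental arm, but the control column stays at 0 and Step 2 applies unchanged.

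**Step 4. Time factor.** Three sessions, each measured at its start and end, give 3 × 2 = 6 cells per person. A single day factor has no place for the before/after contrast. Without it, the two records of a session must be averaged, or one must be discarded.

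**Step 5. Is the sample size affected?** The article gives f = 0.25, alpha 0.05, power 0.95, 2 groups and N = 54. It states no correlation between repeated measures, so ρ = 0.5 is assumed here. For a within-between interaction with m = 2 times, the noncentrality is λ = f²·N·m / (1 − ρ).

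- N = 54: λ = 0.0625 × 54 × 2 / 0.5 = 13.5, with 1 and 52 degrees of freedom; power 0.9501.
- N = 52: λ = 0.0625 × 52 × 2 / 0.5 = 13.0, with 1 and 50 degrees of freedom; power 0.9424.

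So 54 is reproduced as the required N for a two-group, two-time interaction. (If ρ were 0.3 the required N would be 76; if 0.7, 34.) The figure matches the pre/post 2 × 2 model and does not rest on the in-week analysis.

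**The case against.** **The scale name is probably a slip.** Elsewhere in the article VAS-A is paired with STAI-Y1, so STAI-Y2 here is most likely a labelling error. This stands. A reader might infer that a planned outcome is missing altogether, but the documents do not support that: STAI-Y2 is collected in both arms before and after the week and is compared between groups by the 2 × 2 ANOVA. The slip does not restore the Group factor.

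**Table 2 does not split its assessment rows by group, and it marks the intervention period for both arms.** True, but the Other measures, Experimental group and Control group sections do make the split. The scales are also tied to the start and end of training sessions, which controls do not have.

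**Day can stand for session.** The three sessions are spaced through one week, so this is reasonable. What remains is the omitted before/after factor.

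**These are not primary or secondary outcomes.** This stands and limits the weight of the point. STAI-Y1 and VAS-A are there to track affective state during the intervention, which a within-arm analysis can do.

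**An article condenses the full plan.** That would excuse missing detail. Here a specific model, factor and outcome are stated, and the same article's schedule rules them out.

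**Conclusion.** The sentence is wrong as written and should be fixed. With 0 of 30 controls measured in the week, the in-week Group effect and Group × Time interaction cannot be estimated for either scale, and the model omits the before/after factor. This rests only on the article's own schedule and on no assumed figure; ρ = 0.5 enters only the check of N.

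Two stronger readings are tempting. A reader might infer that the trial's efficacy test fails. It does not: the 2 × 2 ANOVA on the PSS, STAI-Y2 and DASS-21 has scheduled data in both arms at both times, and N = 54 is consistent with it. A reader might also infer that anxiety lacks a meaningful controlled comparison because the randomised STAI outcome is the trait form. The documents do not support that either: DASS-21, which includes an anxiety scale, is also a primary measure in both arms, and nothing in the article shows that state anxiety is the construct most likely to change within a week.

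**What to change.** Replace the in-week sentence in the Data analysis section with:

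> In the experimental group only, STAI-Y1 and VAS-A will be analysed with a within-subject model, Session (1–3) × Before/After. Results describe uncontrolled within-session and across-session change and will not be reported as a between-group treatment effect.

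All six cells of this model have scheduled data in the experimental arm, up to 180 records per scale.

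The cost is the rewording of one sentence. No assessment is added, and the sample size and primary analysis do not change. Recruitment was ongoing at submission, so the correction should be made before the in-week data are examined, and recorded by the amendment route that the article describes (registry entry and ethics committees).

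New STAI-Y1 or VAS-A assessments in the control group are not needed to correct the error. They would be a design change during recruitment, and adding them only at baseline and post-intervention would still not make an in-week comparison possible.

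### Five unranked primary scores are each tested at two-sided p < 0.05 with no multiplicity or success rule, while the sample size covers a single test

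*Protocol article*

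**What the plan says.** The Primary outcome measure section lists the PSS-10, the STAI-Y2, the DASS-21 and an ad hoc knowledge questionnaire as the "following questionnaires that will serve as the primary outcome measures". None is placed first. The DASS-21 "is a set of three self-report scales designed to measure depression, anxiety, and stress symptoms", and "The scores for depression, anxiety, and stress are calculated by adding up the scores for the relevant items". No DASS-21 total is described.

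The Data analysis section compares the groups with a 2 × 2 mixed ANOVA (Group by Time, pre and post) and adds: "The analysis will be performed for the PSS, STAY-Y2, and DASS-21". The knowledge questionnaire is not in that list. On the threshold, "Tests of statistical significance and confidence intervals will be two-sided", and a p below "0.05 will be considered statistically significant". The same section also mentions ANOVA for overall improvement across the primary measures, without defining that test or making the separate tests depend on it.

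The Sample size section uses f = 0.25, alpha 0.05, two groups and power 0.95 to reach N = 54, and plans to enrol 60. The nearest thing to a success criterion is in the Discussion, which ties the training's value to "a significant decrease in stress and anxiety and an increase in the knowledge of these conditions".

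**The concern.** Five scores carry primary status into the efficacy ANOVA, and each meets the same unadjusted threshold. Stress is measured twice (PSS-10 and DASS-21 stress) and anxiety twice (STAI-Y2 and DASS-21 anxiety). Nothing says which score decides if the two disagree. DASS-21 depression is also primary, although the Objectives section covers only stress, anxiety and knowledge.

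Without a rule, a reader of the results cannot tell whether one significant score out of five is a positive trial, a mixed one or a chance finding. This matters more here because participants are told their allocation, controls receive no training, and the stress and anxiety scores are all self-reported. The sample size does not reflect the number of tests either: it gives the stated power for one score at 0.05.

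**Working it through.** **Inputs from the article.** Two-sided alpha 0.05 per test, f = 0.25, power 0.95, two groups, N = 54 required and 60 enrolled, 1:1 allocation. Tested primary scores: PSS-10 (1) + STAI-Y2 (1) + DASS-21 scales (3) = 5.

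**Assumptions, not given in the article.** The correlation rho between a participant's pre and post values is taken as 0.5. The correlation r between the change scores of different questionnaires is varied from 0 to 0.9, equal for all pairs.

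**Step 1: the stated sample size.** For the Group by Time interaction with m = 2 measurements, lambda = f² × N × m / (1 − rho), with 1 and N − 2 degrees of freedom. At N = 54, lambda = 0.0625 × 54 × 2 / 0.5 = 13.5, and power at alpha 0.05 is 0.9501. The stated N = 54 is reproduced, so it fits one pre-post test on one score. (With rho = 0.3 the same formula gives 76, and with rho = 0.7 it gives 34.) At the enrolled N = 60, lambda = 15 and power is 0.968.

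**Step 2: chance of at least one p < 0.05 when no score is affected.** For independent scores this is 1 − 0.95^K:
- K = 5: 1 − 0.95^5 = 22.6%
- K = 3 (a single DASS-21 total): 1 − 0.95^3 = 14.3%

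For results favouring VR only, alpha is 0.025 per score, and five scores give 1 − 0.975^5 = 11.9%.

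The correlated cases were simulated: 100,000 trials per setting, 30 per arm, with a two-sided t-test on the pre-post change, which is equivalent to the 2 × 2 interaction test.

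| r | 5 scores, either direction | 5 scores, favouring VR | 3 scores, either direction |
|---|---|---|---|
| 0 (exact) | 22.6% | 11.9% | 14.3% |
| 0.3 | 21.0% | 10.6% | 13.5% |
| 0.5 | 18.3% | 9.1% | 12.3% |
| 0.7 | 15.0% | 7.5% | 11.0% |
| 0.9 | 10.3% | 5.1% | 8.3% |
| One test | 5% | 2.5% | 5% |

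**Step 3: power if three scores are tested with Holm.** The first threshold is 0.05 / 3 = 0.0167. Under the planned ANOVA (f = 0.25, rho = 0.5), power per score is 88.1% at N = 54 and 91.7% at N = 60. Restoring 95% at that threshold would take N = 70.

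**Step 4: power if all three must reach p < 0.05.** Suppose each score has the planned effect. At N = 54 the chance that all three succeed is at least 1 − 3 × (1 − 0.9501) = 85.0%, and 0.9501³ = 85.8% if they are independent. At N = 60 these are 1 − 3 × (1 − 0.968) = 90.4% and 0.968³ = 90.7%. In either case it cannot exceed the single-score power.

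**The case against.** The strongest reply is that the article nowhere says one significant score is enough. Its only success wording, in the Discussion, joins stress, anxiety and knowledge. If all had to succeed, the familywise error would not be inflated. The mention of overall improvement across the primary measures, and an entry for MANOVA in the Abbreviations that is not used elsewhere in the text shown, might point to an omnibus test. Multiplicity detail is often left to an analysis plan, and the Dissemination plans section looks ahead to later confirmatory studies.

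Part of this stands. A reader might infer that the plan permits a claim on any single score; the article does not say so, it simply leaves the matter open. But the Discussion sentence names constructs rather than scores and is not tied to the analysis. The overall test is undefined and gates nothing, and an unused abbreviation is not a method. The article itself fixes both the set of primary measures and the threshold for each, so an analysis plan could repair this only by overriding what is written.

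Two stronger readings should be resisted. A reader might take 15% to 23% as the chance of falsely claiming efficacy. Those figures count significant results in either direction, including any favouring control, and apply only for correlations from 0.7 down to 0. A reader might also count each part of the knowledge questionnaire as a further test and reach about 34% for eight independent scores. The Data analysis section does not list knowledge among the measures to be tested, nor does the article say how its parts would be scored for testing.

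**Conclusion.** The point holds in this form: five unranked primary scores are tested at an unadjusted two-sided 0.05, with no rule for combining them and a sample size for one test. If none is affected, the chance of at least one nominally significant primary result is about 10% to 23% in either direction, or about 5% to 12% in favour of VR, against 5% and 2.5% for a single test. That is roughly a two- to fivefold inflation.

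The range rests on assumed equal correlations from 0.9 down to 0, because the article gives none. The count of five rests on testing the three DASS-21 scales separately, as the outcome section scores them. If a single total were analysed instead, three tests would remain and the two-sided figure would be about 8% to 14%. The inflation applies when any one significant score may be presented as success, which the article neither permits nor rules out.

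**What to change.** Before results are seen, name one primary score for each construct in the objective: stress, anxiety and knowledge. The choice of anxiety scale belongs to the sponsor. The knowledge score needs a defined scoring and a place in the list of analysed measures. Move DASS-21 depression and the duplicate stress and anxiety scales to secondary.

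Then state one of two rules:
- **Separate claims for each construct:** test the three scores with Holm at a familywise two-sided 0.05.
- **The joint claim in the Discussion:** state that all three must reach two-sided p < 0.05. This needs no alpha correction.

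No new data are needed, but there are costs. Under Holm, power per score at the first step is about 88% at N = 54 and 92% at N = 60, rather than 95% and 97%. Under the joint rule each score keeps its 0.05 level, but the chance that all three succeed may be as low as about 85% at N = 54 and 90% at N = 60. Either way the Sample size section should restate the power for the chosen rule and give the assumed rho. Recruitment was already under way at submission, so the change needs a protocol amendment, with the ethics review and registry update that the article requires.
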